**Fig. 4 Fig4:**
[figure not shown]
High-velocity, low-amplitude (HVLA) spine manipulation. **a** HVLA for C7-T4 segments while prone. **b** HVLA for T3 to T8 while prone. **c** HVLA for upper thoracic segments while supine. **d** HVLA for lower thoracic segments while supine. **e** HVLA for lumbar segments in lateral lying. **f** HVLA for the sacroiliac joint in lateral lying

#### Compliance supervision

To promote subject cooperation, the subjects and their parents will be educated before treatment about the risk of progression of scoliosis, its harmfulness, and the necessity for treatment. We will invite the subjects participating in the study to enter the WeChat group we have established, and a coordinator will manage the WeChat group and regularly share information about scoliosis within the group. In the 4-week period of home-based training, the parents will be required to supervise their children’s training and report the daily training intensity using the WeChat check-in procedure. A physiotherapist will monitor the parents’ reports and provide suggestions and encouragement. When a subject’s compliance begins to falter, their parents will be encouraged through WeChat to encourage the subjects to continue training. If the subjects are able to complete the trial, we will provide free scoliosis consultation services until the subjects are 16 years old.

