## Methods/design

### Study design

The study will be a nonblinded pilot RCT with two parallel groups. The protocol will follow the Declaration of Helsinki and will be conducted according to the standard protocol items: recommendations for interventional trials (SPIRIT) guidelines and the World Health Organization trial registration data set (version 1.2.1) guidelines for clinical trial protocols (see Additional file 1 and Additional file 2). It will be conducted in the Rehabilitation Department of Tongji Hospital at Huazhong University of Science and Technology in Wuhan, China. AIS subjects will be recruited from the hospital’s outpatient rehabilitation department. To recruit more subjects, we will post study-related advertisements in the Outpatient department and WeChat app. A flow diagram is shown in Fig. 1.

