### Eligibility

The inclusion criteria will be as follows [33]:
Age of 10–18 years.A diagnosis of idiopathic scoliosis.Cobb angle of 10–25°.Risser sign of 0–2.Agree not to receive any other treatments for scoliosis such as brace and insoles during the study period.

The exclusion criteria will be as follows:
Contraindications for exercise, such as cardiovascular or respiratory insufficiency.Contraindications for SMT, including inflammation, infection, advanced degeneration, congenital malformations, trauma, and cerebrovascular anomalies [34].A history of spinal surgery.A history of scoliosis treatment involving surgery, a brace, exercise, etc.

In addition to the simple unwillingness to continue, factors that can prevent a subject from continuing to participate, such as a new diagnosis of a severe disease, will be considered valid grounds for withdrawal.

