### Randomization and blinding

The physician will explain the whole content of the trial to the candidates who meet the eligibility criteria in a separate room. Written informed consent from both subject and their statutory guardians are required. Their demographic information and medical history will then be recorded.

Each subject will be assigned to either the study or the control group using simple randomization with a 1:1 allocation. The random sequence will be generated by an investigator using an electronic random sequence generator (www.random.org). The numbers in the random sequence will be sealed in consecutively numbered, opaque envelopes. When required, the envelopes will be opened by a person who will not be involved in the intervention, assessment, or statistical analysis.

Due to the nature of the interventions, blinding of the therapists and subjects to the intervention type will be impossible, so only the assessors and those performing the statistical analysis be blinded to the allocation results. To ensure that the group allocation results remain concealed as much as possible, the assessors will process the assessments in a separate room, and the statistical analysis will not include the information about the subjects and their allocations. The schedule for the treatments and outcome assessments is presented in Fig. 2.

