## Discussion

Although AIS has been diagnosed and treated for many years, nonoperative treatment approaches have not been thoroughly investigated [2]. For patients who are skeletally immature, the “watch and wait” approach followed by bracing (when the Cobb angle exceeds 25°) has become the standard treatment in the USA [64], though some Europeans have advocated for more proactive physical therapy interventions to maintain or even reduce curvatures [65, 66]. Due to the lack of scientific evidence, the recommended treatment for mild AIS is only PSSE, but the effect is not always satisfactory [1].

SMT is a popular and effective treatment for nonspecific neck or back pain [20, 21]. Symptoms such as pain and limited mobility can often disappear quickly after SMT, typically after a few weeks of treatment [67]. It is commonly used for scoliosis, but its efficacy remains unclear.

Thus, we designed this pilot RCT to include 2 weeks of SMT and 8 weeks of PSSE. The hope is that the combination can help reduce the Cobb angle, improve trunk symmetry, and improve quality of life to a greater extent than can PSSE alone. Our expectations are not unreasonable because pain and restricted joint mobility in the spine are the common manifestations of spinal dysfunction, including scoliosis. SMT has been shown to be effective in relieving pain along the spine through inhibition mechanisms mediated by the central nervous system [68]. Pain relief reduce movement limitations and helps patients achieve better motor performance. SMT can help improve spine mobility, segmental range of motion, dysfunction of the facet joints, and muscle imbalances [22]. Improved bone alignment and more symmetrical muscle states will lead to a better structural foundation for PSSE. Indeed, there is evidence that SMT can also improve motor performance by improving sensory-motor integration [27–32]. PSSE training after SMT is likely to yield better motor control and improve the efficiency of the exercise [32].

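### A single WeChat group for subjects of both arms of a nonblinded trial is an avoidable channel between arms; arm-specific or private messaging would close it at almost no cost

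*Protocol article*

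**What the plan says.** The Compliance supervision section of the protocol article uses WeChat for three things: a group for subjects, parents' reports on home exercise, and encouragement through the parents when compliance falters. On the group it says: "We will invite the subjects participating in the study to enter the WeChat group we have established". It adds that "a coordinator will manage the WeChat group and regularly share information about scoliosis within the group". In the 4-week home-based phase, parents supervise the exercises and "report the daily training intensity using the WeChat check-in procedure". The group is mentioned in the singular. No division by arm is described, and nothing says whether members may discuss treatment or see each other's check-ins.

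The Study design section states: "The study will be a nonblinded pilot RCT with two parallel groups". Randomization and blinding says that "blinding of the therapists and subjects to the intervention type will be impossible", so that "only the assessors and those performing the statistical analysis be blinded to the allocation results". The same section has a physician explain the entire trial to candidates before they are randomized.

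Against outside treatment, Eligibility requires subjects to "Agree not to receive any other treatments for scoliosis such as brace and insoles during the study period". The Discussion says of spinal manipulative therapy (SMT): "It is commonly used for scoliosis, but its efficacy remains unclear".

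**The concern.** Families in both arms know their allocation, and before treatment they are taught about the risk and harm of progression and the need for treatment. A shared group puts control families, whose children receive exercise only, in contact with families whose children also receive manipulation in the first 2 weeks. Two consequences are possible.

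- **Self-report and behaviour.** Regular contact with the other arm can sharpen a control family's sense of having missed something. That may affect SRS-22 answers, parents' reports of home training, and willingness to continue. Retention and adherence to allocation are named feasibility observations, so the primary outcome is touched as well as the efficacy measures.
- **Outside SMT in controls.** The article itself calls manipulation common in scoliosis. Contact with families receiving it could make it easier to seek. Any such crossover would shrink the between-arm difference.

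The pilot's effect sizes have a further use. The secondary measure with the largest between-group effect is to guide the choice of the full trial's primary outcome, and the effect sizes feed its sample size. Bias in a self-reported candidate, or dilution of an objective one, would carry forward into that planning.

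**Working it through.** The point rests on reading the sections together. The arithmetic at the end is an illustration only.

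**1. Is there one group for both arms?** On the plain reading, yes. The invitation goes to the study's subjects without distinction, and to one established group. No rule separating the arms is stated.

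**2. What does the group add to what families already know?** Candidates hear about the whole trial before randomization, so control families know that a manipulation arm exists and that they are not in it. Both arms also attend supervised outpatient exercise 5 times a week for 4 weeks and may meet there. The group therefore does not create awareness. It adds a standing contact between families, which can continue into the 4-week home phase after the regular supervised sessions have ended.

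**3. Which outcomes are exposed?**
- Exposed: the SRS-22 (self-reported), home training (reported by parents), retention and adherence.
- Largely protected: Cobb angle, 3-D posture and somatosensory evoked potentials, if assessor blinding works as planned. The section on the angle of trunk rotation has a therapist take the reading. That therapist may know the allocation already, but the chat group does not change this.
- Objective measures could be affected only through actual crossover or changed exercise effort.

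**4. Is outside SMT addressed?** Yes, by the entry agreement. Brace and insoles are given as examples, so for a control subject manipulation falls within the barred treatments even though it is not named.

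**5. Illustration of dilution.** Inputs from the Sample size section: d = 1.0 for change in Cobb angle, significance level 5% (sidedness not stated; two-sided taken here), power 80%, 17 per group, 15% dropout, 20 per group.

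Reproducing the plan: a two-sided two-sample t test needs n = 16.71, rounded up to 17 per group, with power 80.7%. With dropout, 17 / 0.85 = 20 per group, or 40 in total. The stated figures reproduce.

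Suppose a share c of controls obtained SMT elsewhere with the full trial effect. Then d(c) = 1.0 × (1 − c), and the noncentrality of the t statistic is d(c) × √(n/2), with √(17/2) = 2.915.

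| Assumed c | d(c) | Noncentrality | Power, 17 per group | n per group for 80% power |
|---|---|---|---|---|
| 0% | 1.00 | 2.92 | 80.7% | 17 |
| 5% | 0.95 | 2.77 | 76.6% | 19 |
| 10% | 0.90 | 2.62 | 72.1% | 21 |
| 20% | 0.80 | 2.33 | 61.9% | 26 |
| 30% | 0.70 | 2.04 | 50.8% | 34 |

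Every c above zero is an assumption with no basis in the documents, and full effect from outside treatment is the extreme case. The table shows how sensitive a comparison of this size is to crossover. It does not show that crossover will occur, or that the chat group would cause it. The self-report effect cannot be sized from the documents.

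**The case against.** The strongest reply is that the chat group changes little. Control families know their allocation and know what the other arm receives. The resulting self-report bias follows from unblinding, which the article calls unavoidable; its limitations section also concedes that the trial is not double-blinded. Arms may meet at the clinic anyway. Outside SMT is barred by the entry agreement. The coordinator manages the group and shares general information; open discussion of treatment is not described. The group is a deliberate compliance measure, and a pilot exists to try such measures out.

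Most of this stands, and it limits the size of the point. It does not remove it. The group is a contact route that the plan itself creates, and the same compliance support can be delivered without it.

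Three stronger readings are tempting but not supported:

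- A reader might infer that the group invites outside SMT. The documents bar such treatment, and the most that can be said is that the group could facilitate it.
- A reader might infer that assessors would be unmasked through posts. Nothing in the article places assessors in the group.
- A reader might infer that outside treatment will go unrecorded, because the home check-in concerns training intensity and the planned calls concern adverse events. A condensed article may leave such recording to the full protocol, so its absence here is not a defect in itself.

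Nor can the power figures be read as an expected loss. They also concern the Cobb angle, which the article treats as secondary to feasibility in its outcome sections. The trial's SMT is a specific course given just before exercise, and outside manipulation need not reproduce its effect.

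**Conclusion.** The point holds as a minor design weakness. As described, subjects of both arms of a nonblinded trial share one WeChat group, and this is an avoidable channel between arms. It can add to existing bias in the SRS-22, parent-reported training, and adherence or retention, and could facilitate outside SMT in controls despite the entry agreement.

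The size is unknown. The two effects could also pull in opposite directions: crossover would shrink the apparent benefit, while discouraged controls could inflate it. The conclusion assumes that the singular group in the article is what is actually run and that members can communicate in it. If it is already a one-way channel, or is split by arm, the point falls away and the article need only say so. No stated figure is wrong, and the planned sample size need not change on this account.

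**What to change.** Replace the shared group by one of two arrangements:

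- two arm-specific WeChat groups, run by the same coordinator with identical content; or
- a coordinator-only broadcast list, with parents' check-ins sent privately to the monitoring physiotherapist.

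In either case, state that outcome assessors are not members.

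As a minor addition, name manipulation among the examples in the existing entry agreement on outside treatment, worded for both arms so that it excepts the allocated SMT. On the telephone calls already planned under Adverse events (daily in the first 2 weeks, then weekly for 6 weeks), ask both arms one question about treatment received outside the trial. That would capture crossover by any route and inform the feasibility judgement on adherence to allocation.

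The cost is a second chat group or a broadcast list, a few words in the agreement, and one question on existing calls. No extra subjects or visits are needed. The downside is some loss of peer support across arms. Support within each arm is kept if two groups are used.

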### Assessment

Age, sex, height, weight, Risser sign, menarche status (for the girls), and type of scoliosis will be recorded at the start of the experiment. The United States Risser staging will be used to quantify skeletal maturity on a scale of 0 to 5 [43]. Stage 0 represents no ossification of the iliac apophysis, whereas stage 5 represents complete ossification and fusion. The scoliosis types will include thoracic, lumbar, thoracolumbar, and S-shaped scoliosis, corresponding to the anatomical site of the spinal deformity [1].

The primary outcome will be the feasibility of performing a full-scale study using these protocols. The time to complete enrollment, recruitment rate, subject retention, and adherence to the treatment allocation will all be important observations. The efficacy of treatment will be the secondary outcome. Spine curvature, rotation of the trunk, and postural symmetry will be assessed by the Cobb angle from X-ray images; the ATR, as measured with a Scoliometer; and 3-DPPs, as measured using a global postural system (GPS), respectively. The SEP will be assessed for evaluating sensorimotor integration, and the SRS-22 will be administered for the quality of life. The Cobb angle will be measured at baseline and at the end of 8 weeks of training. The SEP will be measured at baseline and at the end of 2 weeks of training. The ATR, 3-DPPs, and SRS-22 scores will be measured at baseline and then after 2 weeks, 4 weeks, and 8 weeks of treatment. The mean changes of Cobb angle from baseline to the end will be compared. And the mean difference of other indicators between each two visits will be used for comparative analysis.

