### Data collection, data management, and statistical analysis

The primary outcome measures will be tabulated and interpreted with respect to the goals established a priori.

To estimate the sample size required for a future full-scale RCT, between-group effect sizes and their 95% confidence intervals will be calculated by applying Hedges’ correction. A minimum power of 80% will be used to detect changes in the Cobb angles, ATRs, 3-DPPs and SRS-22 scores (*α* = 0.05). The sample size will be increased to allow for an estimated 20% dropout rate. Statistical methods for the secondary outcome measures will be evaluated via comparisons of changes between groups.

The data will be double entered into EpiData 3.1 software (The EpiData Association, Odense, Denmark) and then transferred to version 22.0 of the SPSS software suite (IBM, Armonk, NY, USA) for the analyses. The threshold for significance will be taken as *α* ≤ 0.05. A statistician who will be blinded to the allocation results will analyze all the data. The continuous variables will be presented as means ± SDs, and the categorical variables will be presented as ratios. The baseline readings will be compared using independent samples *t* tests or chi-squared tests. For the Cobb angles and SRS-22 scores, independent samples *t* tests will be used to compare the two groups, and paired *t* tests will be used for within-group comparisons. For the M, U, MU, and M+U SEP peak amplitudes and latencies, nonparametric Wilcoxon signed-ranks tests will be used to compare these values between and within the groups. For the 3-DPPs and ATR, repeated measured analysis of variance will be used for the between-groups and within-groups comparison. Furthermore, we will perform subgroup analysis by age group (age < 13 years and age ≥ 13 years) [2, 33]. To deal with the missing data, a sensitivity analysis and weighted estimating equations will be used as the primary approach [61].

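### Cobb angle and SRS-22 are compared by unadjusted t tests on change; adjusting for the collected baseline would be more precise unless the baseline to follow-up correlation is very high

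*Protocol article*

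**What the plan says.** Baseline values of both outcomes are available. Under Assessment: "The Cobb angle will be measured at baseline and at the end of 8 weeks of training". For SRS-22: "The ATR, 3-DPPs, and SRS-22 scores will be measured at baseline and then after 2 weeks, 4 weeks, and 8 weeks of treatment".

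The same section fixes the analysis variable. For Cobb angle, "The mean changes of Cobb angle from baseline to the end will be compared". For the rest, "And the mean difference of other indicators between each two visits will be used for comparative analysis".

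The section Data collection, data management, and statistical analysis fixes the test: "For the Cobb angles and SRS-22 scores, independent samples *t* tests will be used to compare the two groups". Its general rule is "Statistical methods for the secondary outcome measures will be evaluated via comparisons of changes between groups". For SRS-22, a t test on change follows from reading these sentences together.

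No baseline covariate is named anywhere. The only stated use of baseline beyond the change score and within-group tests is a between-group check: "The baseline readings will be compared using independent samples" t tests or chi-squared tests. Allocation is by simple 1:1 randomization, with no stratification described (Randomization and blinding).

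**The concern.** A change score subtracts the whole baseline value, however well or badly baseline predicts follow-up. ANCOVA estimates that relation and removes only the part of baseline that carries over. In a trial with about 17 evaluable per arm and unstratified allocation, the difference can show in two linked ways: a wider confidence interval, and an estimate that moves with chance baseline imbalance. Testing baseline for significance corrects neither.

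Efficacy is secondary in this feasibility pilot, but its effect sizes are still used. They size the full trial (Sample size calculation; Data collection, data management, and statistical analysis), and the outcome with the largest between-group effect becomes the candidate primary outcome (Primary outcome measure). Change in Cobb angle also drives the pilot's own sample size and its interim efficacy look.

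**Working it through.** **Inputs from the protocol.** Change in Cobb angle, d = 1.0, significance level 5%, power 80%, 17 per group, 15% dropout, 40 in total (Sample size). Interim look at 20 completers (Interim analysis).

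**Assumptions.** Two-sided test (the sidedness is not stated), equal arms, equal baseline and follow-up variance s², and correlation r over a range, because the documents give none.

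**1. The plan's own figure.** Two-sample t test, n = 17 per group: noncentrality 1.0 × sqrt(17/2) = 2.915 on 32 df, power 0.807. With 16 per group the power is 0.781, so 17 is the minimum. 17/0.85 = 20 per group, 40 in total. The stated figures reproduce.

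**2. Relative variance.** Per subject, the variance of change is 2(1 - r)s² and the ANCOVA residual variance is (1 - r²)s². The ratio is (1 + r)/2. Estimating the baseline slope inflates the ANCOVA variance by 1 + 1/(2n - 4) = 31/30 at n = 17.

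**3. Power at 17 per arm** (noncentral t with effective d = 1/sqrt((1 + r)/2), 31 df and the 31/30 factor; 20,000 simulated trials as a check):

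| r | (1 + r)/2 | × 31/30 | change in SE | ANCOVA power | simulated | n per arm for 80% |
|---|---|---|---|---|---|---|
| 0.5 | 0.750 | 0.775 | -12% | 0.894 | 0.897 | 14 |
| 0.7 | 0.850 | 0.878 | -6% | 0.854 | 0.857 | 15 |
| 0.9 | 0.950 | 0.982 | -1% | 0.813 | 0.808 | 17 |
| 0.95 | 0.975 | 1.008 | about +0.4% | 0.803 | not run | 17 |

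The comparator is 0.807 for the t test on change (simulated 0.811, 0.807 and 0.799 at r = 0.5, 0.7 and 0.9). The variances are equal when (1 + r)/2 × 31/30 = 1, that is r = 60/31 - 1 = 0.935. With the lost degree of freedom, the power advantage ends at about r = 0.93.

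**4. Chance imbalance.** The SE of the baseline difference is sqrt(2/17) = 0.343 SD. P(|difference| > 0.5 SD) = P(|Z| > 1.458) = 0.145. With about 10 per arm at the interim, the SE is sqrt(2/10) = 0.447 SD and the probability is about 0.26.

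The change score keeps (1 - r) times the imbalance. At r = 0.7 and 0.5 SD this is 0.3 × 0.5 = 0.15 baseline SD. The SD of change is sqrt(2 × 0.3) = 0.775 baseline SD, so the shift is 0.15/0.775 = 0.19 in d. In the simulation, the change-score estimate correlated with baseline imbalance at -0.50, -0.38 and -0.23 for r = 0.5, 0.7 and 0.9.

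**5. Illustration for the full trial.** If the change-score effect were d = 0.5, a t test on change needs 64 per arm for 80% power, before dropout. ANCOVA needs 49, 55 or 62 at r = 0.5, 0.7 or 0.9.

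**The case against.** The strongest reply is that nothing here is wrong. Under randomization the t test on change is valid and unbiased on average (simulated mean d about 1.00), it matches the endpoint used for sizing, and it delivers the planned power. That stands. A reader might infer that the trial is underpowered or its sample size mistaken; step 1 shows otherwise.

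A reader might also infer that ANCOVA has the smaller variance at any correlation below 1. That is a large-sample statement and fails at 17 per arm above about r = 0.935. An angle re-measured after 8 weeks may well have a high r. The restriction of eligibility to 10–25° may pull r down, but the documents settle neither.

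Nor is a material imbalance likely: 14.5% is a minority risk. The 0.19 shift in d should be read against an SE of d of about sqrt(2/17 + 1/68) = 0.36. It is ordinary sampling error, which the planned 95% confidence interval already covers. The wider interval and the residual imbalance are largely one effect seen twice.

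For SRS-22, the power figures above use the Cobb planning value and do not carry over. SRS-22 is measured at four visits, so a visit must be chosen. Its dimension on satisfaction with treatment has a doubtful baseline in patients who are excluded if previously treated.

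What survives is that the article itself names both the analysis variable and the test, so this is not a detail left to an unseen analysis plan, and a better use of data already collected is available.

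**Conclusion.** The point holds as an avoidable loss of precision; it is not an error of validity. At 17 per arm the gain from baseline adjustment is about 9 percentage points of power at r = 0.5, about 5 at r = 0.7 and under 1 at r = 0.9. It vanishes at about r = 0.93 and is slightly negative at 0.95 (0.803 against 0.807). These figures rest on an assumed r, equal variances, equal arms and a two-sided test. The conditional shift from imbalance is (1 - r) times the realised baseline difference.

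The change is worth making because these effect sizes choose the endpoint and the size of the full trial, and because the possible loss is negligible. The documents do not support calling the planned analysis biased or the sample size wrong.

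**What to change.** - Analyse week-8 Cobb angle by ANCOVA with arm and baseline Cobb angle. Use the same model for the Cobb comparison at the interim analysis, so that the stopping test and the final test agree.
- Analyse week-8 SRS-22 scores in the same way, limited to those with a meaningful baseline, and say how the satisfaction dimension is handled.
- Report the adjusted difference with its 95% confidence interval, the raw SD and the observed r.
- State which SD (raw, change or residual) standardises the effect size. An effect scaled by the residual SD is not interchangeable with the change-score d used in the Sample size section.
- Plan the full trial with the same model that will analyse it.
- Keep the t test on change as a supportive analysis.

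This needs revised wording for the final analysis, the interim analysis and the effect-size calculation. It needs no new data or patients. The statistical cost is one degree of freedom, with a negligible loss if r proves very high.
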